### Mediation analysis

We will use causal mediation analysis to understand the mechanisms by which the internet-based pain education and exercise exerts its effects on the primary outcome, pain intensity at 8 weeks. The proposed intervention aims to reduce kinesiophobia, pain catastrophising, and improve self-efficacy, and pain-related attitudes and beliefs post-treatment. It is hypothesised that short term effects of these putative mediators will cause reduction in pain intensity at 8 weeks. We will estimate indirect effects of the intervention via the putative mediators, and path specific effects (intervention-mediator and mediator-outcome). We will use directed acyclic graphs to identify the minimum sufficient set of confounders that will need to be adjusted. These directed acyclic graphs will be registered before data collection begins. We will use sensitivity analyses to explore how much residual confounding would explain away the indirect effect, if one is detected. We will use the ‘mediation’ R package to conduct these analyses [42].

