**Methods:**

This is a prospectively registered, assessor-blinded, two-arm randomised controlled trial with economic evaluation comparing the Internet-based pain education and exercise intervention with a control group that will receive an online booklet. One hundred and sixty patients will be recruited from Sao Paulo, Brazil. Follow-ups will be conducted in post-treatment, 6 and 12 months after randomisation. The conduct of the study, as well as the evaluations and follow-ups will be carried out entirely remotely, through online platforms and telephone calls. The primary outcome will be pain intensity at post-treatment (8 weeks) measured using the 11-item Pain Numerical Rating Scale. Secondary outcomes will be biopsychosocial factors presents in the chronic musculoskeletal pain condition. Costs due to chronic musculoskeletal pain will be also measured, and cost-effectiveness analysis from a societal perspective will performed.

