### Procedure

The blinded assessor will screen potential participants to determine eligibility. Eligible patients will receive the online consent form and will be informed about the aims of the study. The blinded assessor will then collect the patient’s sociodemographic data, medical history, and the data related to the study outcomes for baseline assessment. The baseline assessment will be performed via videoconference using a personalised link using Whereby platform. All other assessments will be collected by telephone calls, smartphone messages or e-mail (8 weeks, 6, and 12 months after randomisation) through a questionnaire created on the Typeform platform (Fig. 1). All data entry will be coded and double-entered into a Microsoft Excel spreadsheet. A second blinded researcher will double-check the data prior to the analysis.

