### Outcome measures

The primary outcome will be pain intensity at 8 weeks measured using the Pain Numerical Rating Scale [30], a numerical scale where 0 indicates no pain and 10 indicates maximum pain intensity.

The secondary outcomes will be as follows:
Pain intensity at 6 and 12 months follow-ups;Function at all time points, measured with the Patient Specific Functional Scale [30], a self-reported scale specific for the measurement of functionality, where the patient nominates activities relevant to them and rates their ability to perform each activity on a 0 to 10 scale, with 0 representing “unable to perform activity” and 10 represents “able to perform at the same level as before injury or problem”;Health-related quality of life at all time points, measured with the SF-12 [31], a self-reported questionnaire with 12 questions and classification of 8 different dimensions related to quality of life. Higher scores reflect better quality of life;Kinesiophobia at all time points, measured with the Tampa Scale of Kinesiophobia [32], a self-reported questionnaire with 17 items scored on a four point likert agreement scale (“totally disagree” “partially disagree”, “partially agree”, “totally agree”. Three items [4, 8, 12] are reverse scored. Higher scores on Tampa reflect higher kinesiophobia;Global perceived effect at all time points, measured with the Global Perceived Effect Scale [30], a self-reported scale, with scores of − 5 to + 5, where the progression of the patient’s condition will be classified from a certain point in time. Scores of − 5 indicate the condition is vastly worse while scores of + 5 indicates completely recovered.Anxiety and depression at all time points, measured by the Hospital Anxiety and Depression Scale [33], a self-reported scale with 14 items, 7 for depression and 7 for anxiety. Each item is scored on 0 to 3 scale. Higher scores indicate higher depression or anxiety.Pain catastrophisation at all time points, measured with the Pain Catastrophising Scale [34], a self-reported scale with 13 statements, where the patient ranks the affirmations between 0 being “minimal” to 4 “very intense.” The calculation of the final score is based on 3 subdomains of the scale and higher scores represent higher catastrophising.Pain-related attitudes and beliefs at all time points, measured with the Short Form Orebro Musculoskeletal Pain Questionnaire [35], with 10 items related to musculoskeletal pain each scored from 0 to 10 with total score ranging from 0 to 100. Patients with scores between 51 and 100 points are classified as high risk of developing long-term disability.Self-efficacy at all time points, measured with Pain Self-Efficacy Questionnaire [36], a questionnaire with 22 questions classified in three domains, with a score of each domain ranging from 10 to 100. A total score close to 300 indicates a greater sense of self-efficacy.Adverse events measured by recording the number of adverse events during the intervention period.

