
We will also assess the patient’s expectancy for improvement at baseline using the Expectancy of Improvement Numerical Scale [37].

The same outcome measures will be used at the baseline assessment, post-intervention (8 weeks), 6 and 12 months after randomisation.

Eligible participants will be randomly allocated to one of the treatment groups through an electronic platform. After baseline screening, patients will receive a login and password to access the study website. When the patient logs on to the website, he/she will be randomly allocated to one of the two study groups. The assessor who will confirm the eligibility will be unaware about patients’ allocation.

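### The causal mediation analysis takes mediators and pain from the same 8-week assessment, so it cannot tell mediators reducing pain from less pain improving the mediators

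*Protocol article*

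**What the plan says.** The Mediation analysis section of the protocol article sets out to explain how the intervention "exerts its effects on the primary outcome, pain intensity at 8 weeks". It names four targets: the intervention "aims to reduce kinesiophobia, pain catastrophising, and improve self-efficacy, and pain-related attitudes and beliefs post-treatment". The hypothesis is directional: "It is hypothesised that short term effects of these putative mediators will cause reduction in pain intensity at 8 weeks".

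The abstract (Methods) shows that post-treatment means week 8: "The primary outcome will be pain intensity at post-treatment (8 weeks", and the Outcome measures section agrees: "The primary outcome will be pain intensity at 8 weeks measured using the Pain Numerical Rating Scale". The assessment schedule for every outcome measure, the four mediators included, is: "The same outcome measures will be used at the baseline assessment, post-intervention (8 weeks), 6 and 12 months after randomisation". The Procedure section gives the same times for everything after baseline: "All other assessments will be collected by telephone calls, smartphone messages or e-mail (8 weeks, 6, and 12 months after randomisation".

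Two safeguards are named. Directed acyclic graphs, to be registered before data collection, will select the confounders. A sensitivity analysis will "explore how much residual confounding would explain away the indirect effect, if one is detected".

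**The concern.** Mediation needs the mediator to change before the outcome. Here the first mediator score after randomisation comes from the same assessment as the pain score it is meant to explain.

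Randomisation protects two of the three paths, treatment to mediator and treatment to pain. It does not protect the path from mediator to pain. If treatment lowers pain by some other route, and people with less pain then report less fear and catastrophising and more confidence, the same-visit analysis shows an indirect effect although the mediators did nothing. The report could then credit pain education with a mechanism that the data cannot separate from its reverse.

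**Working it through.** **Timing, from the text**

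| Item | Time | Section |
|---|---|---|
| Mediation outcome (pain) | 8 weeks | Mediation analysis; Outcome measures |
| Mediators | post-treatment, i.e. 8 weeks | Mediation analysis; abstract |
| All measurement times | baseline, 8 weeks, 6 and 12 months | Outcome measures; Procedure |

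No mediator value lies between randomisation and the 8-week pain score.

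**Do the safeguards cover the reverse path?** A directed acyclic graph assumes the direction of each arrow and does not test it. The sensitivity analysis, as worded, concerns unmeasured common causes of mediator and outcome. Neither checks an arrow from pain to mediator.

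**Size.** The plan gives no figure to reproduce, so this is an illustration. From the plan: effect d = 1.5/2.75 = 0.545 SD, and 80 × 0.85 = 68 completers per arm, N = 136. Assumed, in SD units, with X = 1 for the intervention:

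- 8-week pain = −d·X + 0.5·baseline pain + noise, noise variance σ² = 0.75
- 8-week mediator = r·(8-week pain) + 0.4·baseline mediator + noise, noise variance τ² = 0.49
- effect of mediator on pain = 0

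Adjusting for both baseline values:

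- treatment to mediator: a = −r·d, standard error √(4V/N), where V = r²σ² + τ²
- mediator to pain: b = rσ²/V, standard error √[(σ²τ²/V)/(N·V)]
- spurious proportion mediated: a·b/(−d) = r²σ²/V

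| r | r²σ² | V | Proportion mediated | P(a significant) | P(b significant) | Both |
|---|---|---|---|---|---|---|
| 0.2 | 0.0300 | 0.5200 | 5.8% | 0.143 | 0.823 | 11.7% |
| 0.3 | 0.0675 | 0.5575 | 12.1% | 0.248 | 0.991 | 24.6% |
| 0.4 | 0.1200 | 0.6100 | 19.7% | 0.370 | 1.000 | 37.0% |
| 0.5 | 0.1875 | 0.6775 | 27.7% | 0.488 | 1.000 | 48.8% |

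For r = 0.5: a = −0.5 × 0.545 = −0.2725; standard error √(4 × 0.6775/136) = 0.141; z = 1.93; the chance of passing 1.96 is 0.488. A simulation with the same values gave 49% and 28%. Simulations with other noise and baseline values gave about 6% to 7% at r = 0.2 and 37% to 48% at r = 0.5, with 4% to 27% spuriously mediated. With no reverse effect the rate was about 0%. All rates are per mediator, and there are four.

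**Does moving the outcome to 6 months cure it?** Let 6-month pain = k·(8-week pain) + noise, still with no mediator effect. Adjusting for baseline values only, the mediator coefficient becomes k·b and the total effect −k·d. The proportion mediated is a·k·b/(−k·d) = r²σ²/V, the same as before for any k, because 8-week pain is now a common cause of the mediator and of later pain. In simulation with k = 0.7 and r = 0.2/0.3/0.4/0.5, zero was wrongly excluded in 3/12/29/42% of trials, against 7/18/35/44% for the same-visit analysis. Adding 8-week pain to the outcome model makes the expected mediator coefficient 0, and the simulated rate fell to about 2% or less.

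**The case against.** The best reply has four parts.

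- **The analysis is secondary.** It leaves the primary estimate, the sample size, the economic evaluation and participant safety alone. This stands and sets the grade.
- **The size is assumed.** No value of r, and no noise or baseline coefficient, is in the protocol. At r = 0.2 the false-positive rate ranges from about 5% to 12% across settings, which is modest. This stands too: the figures show that baseline adjustment does not remove the problem, and they do not predict this trial's error rate.
- **Six-month pain is a different question.** The plan asks what mediates the effect at 8 weeks, and 6-month pain is a secondary outcome. True, and a reason to keep the 8-week analysis as exploratory.
- **Material is unseen.** The registered graphs and the schedule figure are not shown. The graphs might state the assumed direction, but they cannot create an earlier measurement. The text of two sections gives the measurement times explicitly.

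A reader might go further and infer that the mediators do not work, or that any indirect effect found would be false. The documents do not support that. The same-visit data are compatible with either direction, so the indirect effect could be biased but need not be. A reader might also infer that 6-month pain alone supplies the time order; the working shows that it does not.

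**Conclusion.** The timing flaw holds on the text as written: the mediators and the outcome share one assessment, there is no earlier mediator value after randomisation, and no planned step checks the reverse path. The causal mechanism claim is therefore not supported as planned. An analysis plan cannot repair this by adding detail to the 8-week/8-week analysis.

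The size is illustrative: a false indirect effect in roughly 5% to 50% of trials and about 4% to 27% spuriously mediated. It rests on 68 completers per arm, an effect of 1.5/2.75 SD, no true mediator effect and a reverse effect between 0.2 and 0.5 SD.

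This should be fixed, but it is not a condition for the trial to proceed. Only the mediation analysis is affected, and the primary comparison stands.

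**What to change.** 1. Keep the 8-week/8-week analysis, label it exploratory, state that mediators and pain come from one assessment so that direction cannot be established, and drop the causal wording for it.
2. Add, as the analysis behind any mechanism claim, 8-week mediators to pain at 6 months. Adjust in the main model for baseline pain, baseline mediator and 8-week pain. A lagged model without 8-week pain keeps the same bias and should not be the main model.
3. Update and re-register the directed acyclic graph before results by group are seen, with 8-week pain shown as affected by treatment and as a cause of both the mediator and later pain.

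**Cost.** Text and a revised graph; no new data, since 6-month pain is already collected. Three downsides should be stated. Because 8-week pain is itself affected by treatment, the adjusted estimate leaves out any mediated effect that passes through it, and the plan should say so when it names the effect being estimated. The mediation outcome moves to a secondary time point. Precision may be lower, because the 6-month effect may be smaller and loss to follow-up higher.

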## Discussion

We hypothesise that the telerehabilitation program will benefit patients with chronic musculoskeletal pain by reducing pain intensity and improving function, and psychological and behavioral outcomes (i.e., anxiety, depression, fear-avoidance, catastrophising) compared an online minimal intervention approach (booklet). We also hypothesise that the telerehabilitation program will be a cost-effective intervention compared to the control intervention for patients with chronic musculoskeletal pain. As patients usually support the use of telerehabilitation to improve access to care, we expect that the program will be well received by the patients.

The program is based on relatively simple interventions (i.e., home-based exercise and pain education), although some support is necessary from the coach. This program was designed to be simple to facilitate its implementation in healthcare settings. The program has the potential to change lives of millions of people with chronic musculoskeletal pain that are everyday waiting for treatment in overpopulated cities in Brazil. If the results of our study prove our hypothesis about the effects of treatment on patients with chronic pain, we can contribute to the discussion of a new perspective of this treatment modality for public and supplementary health. The results of the study may serve as a basis for decision making and possible implementation of this therapeutic modality in the treatment of chronic musculoskeletal pain. The economic evaliation present in the study may provide an observation of an important aspect for the implementation of telerehabilitation in the health system. The possibility of reducing health costs would also make it possible to reallocate investments in healthcare.

## Data Availability

All data will be used only for analysis of the present study and will be protected from any unnecessary exposure. The Consent Form according to the Research Ethics Committee of Universidade Cidade de São Paulo was signed by the authors and patients. The paper information will be kept in binders that will be handled only by the researchers responsible for the study and will be kept in locations that will be accessible only to researchers responsible for data analysis. The online information will be able to the researchers in a personal computer located in the personal room of the researcher responsible for the project. All online information will be assessed just by the responsible researchers of specific part of the data analysis. All information will be published confidentially, without the name of the subjects exposed. All data will be available for review and confirmation of data analysis when requested by a review process for publication of the article in indexed scientific journals or presentations at scientific events.

## Abbreviations

SPIRIT: Standard Protocol Items: Recommendations for Interventional Trials.
CONSORT: Consolidated Standards of Reporting Trials
